Cause-specific mortality rate: a physician panel, blinded to group allocation, will adjudicate the cause of death among study participants. The focus will be placed on respiratory-related mortality, which is most relevant to the conditions targeted by the AI modules.Length of hospital stay: evaluate whether the use of the AI-assisted system shortens hospitalization duration, particularly by enabling earlier detection of tube misplacement and pneumothorax, leading to timely treatment.Time to misplacement detection: determine whether the AI system reduces the time required to identify misplaced tubes or pneumothorax, thereby enhancing the timeliness of clinical interventions.Time to reposition ETT and NGT, and time to place a chest drain for pneumothorax.Direct medical costs (eg, x-ray examinations, intubation fees, and hospitalization costs) and indirect medical costs (eg, CAD system costs and labor costs).

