### Determination of Sample Size

The primary outcome of the trial is to assess whether the CAD system can reduce in-hospital mortality. On the basis of data from the NTUH institutional database [19], the ICU mortality rate in 2023 to 2024 is estimated at 28%. A projected reduction to 25% was used for the sample size calculation. With an intraclass correlation coefficient of 0.01, a power of 80%, and a 1-sided α of 5%, each group requires 5450 patients, resulting in a total sample size of 10,900. This design is expected to provide sufficient power to detect clinically significant improvements in patient outcomes (Figure 3).

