**Figure 3 figure3:**
[figure not shown]
Illustration of study design. AI: artificial intelligence; FJCUH: Fu Jen Catholic University Hospital; ICU: intensive care unit; NTUH: National Taiwan University Hospital.

Because the causes of death in patients admitted in ICU may not necessarily be related to CXRs, adjustments to the primary outcome of the formal trial will be made following the pilot testing. This will involve evaluating and modifying the primary outcome (eg, time to detection of misplacement) to better align with the trial’s objectives and needs.

The conduct and reporting of the trial follow the CONSORT (Consolidated Standards of Reporting Trials) 2010 statement with the extension to cluster randomized trials [20].

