### Statistical and Cost-Effectiveness Analysis

Statistical analysis will be conducted using SAS software (SAS Institute) to evaluate the outcomes of this study. Continuous variables, such as clinical outcomes and procedural times, will be summarized using descriptive statistics, including the number of observations, mean, median, SD, range, and 95% CIs. For categorical variables, frequency counts and percentages will be used to summarize the data.

In terms of clinical effectiveness, the primary outcome will be in-hospital mortality, and a proportional test will be used to compare the mortality rates between ICUs that have implemented the AI-assisted detection system and those that have not. The secondary clinical outcomes, which include the length of stay in the hospital, time to detect tube misplacements, and the time taken for medical interventions (such as repositioning of ETT and NGT and placement of pneumothorax drainage), will be analyzed using *t* tests for continuous variables. For categorical outcomes, including the rates of misplacement and other related interventions, chi-square test will be used. In addition, proportional tests will be conducted to examine the differences in the frequency of interventions across the 2 groups.

The study will also incorporate a health care technology and economic evaluation framework to assess the cost-effectiveness of the AI system alongside its clinical effectiveness. This evaluation will explore whether the clinical benefits derived from the AI system justify the associated resource consumption. Previous research by the team [21], such as the use of Markov models in gastric cancer screening and prevention, has demonstrated the utility of such economic evaluations, particularly in quantifying the cost-effectiveness of medical interventions and their impact on mortality reduction.

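### Plain t tests for detection and intervention times ignore the 18 randomised units, and can lose power if the times are right-skewed

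*Protocol article*

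**What the plan says.** The Statistical and Cost-Effectiveness Analysis section of the protocol article groups length of stay with "time to detect tube misplacements, and the time taken for medical interventions" and states that they "will be analyzed using *t* tests for continuous variables". It names no transformation, rank method, time-to-event method or term for the unit. Medians appear only among the descriptive summaries, "including the number of observations, mean, median, SD, range, and 95% CIs".

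The Research Design section sets out what these outcomes are. One aim is to "determine whether the AI system reduces the time required to identify misplaced tubes or pneumothorax". The next outcome is "Time to reposition ETT and NGT, and time to place a chest drain for pneumothorax". That section also fixes 18 ICU units as the units of randomisation.

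The text after Figure 3 says that the primary outcome may be changed after the pilot, by "modifying the primary outcome (eg, time to detection of misplacement"). The cost-effectiveness text lists reduced diagnostic time among the effectiveness measures for the incremental cost-effectiveness ratio (ICER).

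**The concern.** These outcomes are the closest to what the CAD does: it reads the film and sends an alert. One of them may become the primary outcome. The method named for them deserves scrutiny for two reasons.

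First, randomisation is by unit, and patients in one unit share staff and routines. A two-sample t test on patients treats them as independent, so its standard error is too small whenever units differ.

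Second, a time from film to recognition or intervention is bounded at zero with an open right tail. If that tail is long, a few delays dominate the mean and the SD. A comparison of means is then a weak way to show a proportional shortening. The total of 10,900 patients is no protection in itself, because eligibility covers all adults needing a film for a tube or ventilator, and these times exist only for the affected subset.

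At stake is either a false claim of faster detection or a real shortening that goes unseen.

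**Working it through.** **Inputs from the protocol article.** There are 18 units, taken as 9 per arm; the total is 10,900 patients; the test is a t test. The article gives no SD, distribution, misplacement rate, pneumothorax rate or power for the time outcomes. Its only sample size, 5450 per group, is for mortality, so there is no stated figure to reproduce here.

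**Assumptions.** Times are lognormal with log-scale SD s from 0.5 to 1.5. There are 30 affected patients per unit (18 × 30 = 540, or 540/10,900 = 5.0% of patients). The log-scale ICC is 0.02 or 0.05. The CAD multiplies times by 0.70. Tests are two-sided at 5%.

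**Step 1: efficiency of the raw scale.** For lognormal times and a proportional effect, the efficiency of a raw-scale t test relative to a log-scale one is s²/(exp(s²) − 1):

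- s = 0.5: 0.25/0.284 = 0.88
- s = 0.75: 0.5625/0.755 = 0.75
- s = 1.0: 1/1.718 = 0.58
- s = 1.25: 1.5625/3.771 = 0.41
- s = 1.5: 2.25/8.488 = 0.27

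The number of patients does not enter this formula.

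**Step 2: power with the units respected.** Simulated t tests on 9 vs 9 unit means, ICC 0.02:

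| log-SD | raw | log | gap (points) |
|---|---|---|---|
| 0.75 | 96% | 99% | 3 |
| 1.0 | 73% | 88% | 15 |
| 1.25 | 47% | 71% | 24 |
| 1.5 | 29% | 55% | 26 |

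At log-SD 0.5 both are about 100%. Type I error of both unit-mean tests is about 4-5%, so the log gain does not come from an inflated error rate.

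**Step 3: more affected patients.** At log-SD 1.0, 60 per unit gives 90% vs 96% and 100 per unit gives 95% vs 98%. At log-SD 1.5, 100 per unit still gives 54% vs 78%.

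**Step 4: a different effect shape.** Suppose instead that the CAD removes three quarters of the excess above the control 75th percentile and changes nothing below it. Power is then about 65% raw vs 15% log at log-SD 1.0, and 68% vs 12% at 1.5. The ranking reverses.

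**Step 5: ignoring the units.** For a patient-level t test on untransformed times with no true effect, simulated type I error is about 7-11% at ICC 0.02 and 10-19% at ICC 0.05. As a hand check on the log scale, the design effects are 1 + 29 × 0.02 = 1.58 and 1 + 29 × 0.05 = 2.45. The nominal cut-off of 1.96 becomes 1.96/√1.58 = 1.56 and 1.96/√2.45 = 1.25, which correspond to two-sided error rates of about 12% and 21%. Moving to log times at patient level therefore does not cure this; the unit has to be in the analysis.

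**The case against.** The strongest reply is that the article gives no distribution, SD or event rate. Strong skew and a small subset are then plausible but undocumented, and the raw scale is itself inferred: a t test on log times is still a t test, and an analysis plan not shown could specify it. This stands in part. The sizes above are conditional and are shown as a range for that reason. But the article does name the test, and its ordinary reading is untransformed times compared between patients.

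A second reply is that a proportional effect is an assumption. An alert could work mainly by cutting long delays, and step 4 shows that the log scale would then be much the worse choice. The Background section itself presents delayed management of pneumothorax as dangerous, so long delays are not noise. This stands, and it is why the mean difference should not be dropped. The ICER also needs it, since a ratio of geometric means cannot serve there.

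A third reply is that the pilot collects detection times, so the distribution will be known before any change of primary outcome. That also stands, and it supplies the means of settling the scale.

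Two stronger readings are tempting. One is that skew makes the t test invalid. It does not: with reasonable numbers it remains a comparison of means, and the unit-mean version held its error rate. The other is that the small subset causes the loss. A small subset lowers power under every test, and the relative loss in step 1 does not depend on it.

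**Conclusion.** The point holds in a limited form. The firmer part is the missing allowance for the units: under the assumed 30 affected patients per unit, a nominal 5% test runs at about 7-11% (ICC 0.02) or 10-19% (ICC 0.05). That is a matter of validity.

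The scale of analysis is a matter of efficiency. Under a proportional 30% shortening, the raw scale costs about 3 points of power at log-SD 0.75 and 15 to 26 points at 1.0 to 1.5. With mild skew or many affected patients the loss is small, and with benefit confined to long delays it becomes a gain. A reader might infer that the plan certainly wastes much of its power on these outcomes. The article does not support that, because the skew, the event rate and the shape of the effect are all unstated.

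The change is worth making before phase 2, chiefly because time to detection is the article's own example of a replacement primary outcome.

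**What to change.** For time to detection, repositioning and chest drain placement, replace the t tests with a model containing a random unit effect and the randomisation stratum, with small-sample degrees of freedom suited to 18 units. Take log time as the main scale and report the ratio of geometric means with a 95% CI, with medians as description. Confirm the scale from the pooled pilot times, without any comparison by CAD use, before phase 2 starts in January 2026.

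Report the arithmetic mean difference as well, with an interval computed at unit level (for example a bootstrap that resamples units). It feeds the ICER and shows any benefit in the longest delays.

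The cost is analysis wording only, with no extra patients or data. The small downside is that the main effect becomes a ratio, which is less sensitive to benefit confined to the longest delays.

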## Methods

### Research Design

This study adopts a 2-phase design, beginning with a pilot study followed by a multicenter cluster randomized clinical trial. The pilot phase focuses on integrating a CXR CAD system into the hospital’s medical information systems, ensuring smooth functionality within the clinical workflow. The system will undergo testing and initial evaluations in the emergency intensive care and ICU at NTUH over a period of 6 to 12 months.

Building on the pilot phase, the multicenter clinical trial involves ICUs from NTUH, FJCUH, and MSGH. A total of 18 ICU units will participate, with NTUH contributing 14 units and the remaining hospitals contributing 2 units each. These units will be randomized into AI-assisted and control groups. Stratification is based on ventilator use, with randomization conducted within each stratum using uniform distribution. The AI-assisted group allows physicians to access real-time predictions from the CAD system during patient care. These predictions, generated within seconds, focus on identifying critical conditions, such as NGT misplacement, ETT misplacement, and pneumothorax. However, physicians in the control group will adhere to standard procedures without viewing AI-generated predictions, though the CAD system will still analyze images for internal validation. To minimize potential bias, both the outcome assessors and data analysts will remain blinded to group allocation throughout the data collection and statistical analysis phases.

The primary outcome is patient all-cause mortality rate: Assess whether the in-hospital mortality rate decreases after the intervention, reflecting the AI-assisted detection system’s ability to identify life-threatening conditions in a timely manner and facilitate rapid clinical intervention.

The secondary outcomes are as follows:

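### The t tests on detection and treatment times can use only findings that were detected and treated, which the CAD itself changes, so the two arms are compared on different findings

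*Protocol article*

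**What the plan says.** The secondary outcomes listed under Research Design include "Time to misplacement detection: determine whether the AI system reduces the time required to identify misplaced tubes or pneumothorax" and "Time to reposition ETT and NGT, and time to place a chest drain for pneumothorax". Under Statistical and Cost-Effectiveness Analysis these times, given there as "time to detect tube misplacements, and the time taken for medical interventions (such as repositioning of ETT and NGT and placement of pneumothorax drainage", together with length of stay, "will be analyzed using *t* tests for continuous variables". The same section handles occurrence separately: "For categorical outcomes, including the rates of misplacement and other related interventions, chi-square test will be used". It adds proportion tests on how often interventions were carried out.

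Control physicians do not see the predictions, "though the CAD system will still analyze images for internal validation". That use is not linked to the time outcomes. Both descriptions of data collection state that images are not collected.

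The text after Figure 3 foresees, once the pilot is done, "evaluating and modifying the primary outcome (eg, time to detection of misplacement". The article does not state which findings enter the time comparison, when the clock starts, or how a finding is counted if it is never noticed, never acted on, or cut off by death, discharge or tube removal.

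**The concern.** A t test needs one observed time per case. A misplaced tube that nobody notices has no detection time. A patient who dies, is discharged, has the tube removed or is managed without a drain has no repositioning or drain time. With the named method and no other rule, these cases cannot contribute.

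Whether a finding is detected or acted on is itself an effect of the intervention. The AI Detection Tool section has the CAD flag findings and notify the physician, and the economic section counts fewer misdiagnoses among the benefits. If CAD units detect findings that control units miss, or the reverse, the samples differ in case mix. Randomising units does not protect a comparison that conditions on something that happens after randomisation. This problem is separate from skewness, power and clustering.

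These are the outcomes on which the CAD acts most directly. Detection time may become primary, and reduced diagnostic time is also one of the effectiveness measures for the cost-effectiveness ratio.

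**Working it through.** **Inputs.** The protocol states no mean, SD, detection rate or power for these times, so there is no figure to reproduce. All times and shares below are assumptions, chosen to show the mechanism and its range.

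**Illustration A.** 70% of findings are easy and 30% hard. Control finds the easy ones in a mean of 2 h and none of the hard ones. CAD finds the easy ones in 1.5 h and 5/6 of the hard ones (25% of all findings) in 4 h.

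- Detected only, control: 2.00 h.
- Detected only, CAD: (0.70×1.5 + 0.25×4)/0.95 = 2.16 h, so CAD looks 0.16 h slower.
- All findings, missed ones held at 24 h, control: 0.70×2 + 0.30×24 = 8.60 h.
- All findings, CAD: 0.70×1.5 + 0.25×4 + 0.05×24 = 3.25 h, a gain of 5.35 h.

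**Range of A and condition for reversal.** Let s be the hard share (missed in control) and h the CAD time for hard findings.

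- Detected-only difference: [1.5(1−s) + (5/6)sh]/(1−s/6) − 2. For s from 10% to 40% and h from 2 to 6 h it runs from −0.46 to +1.11 h.
- All-findings gain: 0.5(1−s) + 20s − (5/6)sh. Over the same grid it runs from 1.95 to 7.63 h.
- The detected-only difference turns positive only if h > 0.6/s + 1.4, that is above 7.4 h at s = 10%, 4.4 h at 20%, 3.4 h at 30% and 2.9 h at 40%. At 10% missed, no reversal occurs anywhere in this grid.

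**Illustration B, partial detection in control.** 70% of findings are easy (mean 1 h, always found) and 30% hard (mean 6 h). Control finds a share d of the hard ones and CAD finds 90%. CAD multiplies all times by f.

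- Detected only: control (0.7 + 1.8d)/(0.7 + 0.3d); CAD f×2.32/0.97.
- All findings to 24 h: control 0.7 + 0.3[6d + 24(1−d)]; CAD 2.32f + 0.72.

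| d | f | Detected only: control / CAD (h) | All findings: control / CAD (h) |
|---|---|---|---|
| 0.4 | 1.0 | 1.73 / 2.39 | 5.74 / 3.04 |
| 0.4 | 0.8 | 1.73 / 1.91 | 5.74 / 2.58 |
| 0.6 | 0.8 | 2.02 / 1.91 | 4.66 / 2.58 |
| 0.8 | 0.6 | 2.28 / 1.44 | 3.58 / 2.11 |

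The first two rows reverse the sign, the third almost hides the benefit, and the fourth has the right direction.

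**Simulated t tests under B** (Welch, 5% two-sided, 300 true findings per arm, lognormal times, 2000 runs, clustering ignored).

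- Speed unchanged: CAD is declared significantly slower in 95, 80, 58, 32, 16 and 7% of runs at d = 0.3, 0.4, 0.5, 0.6, 0.7 and 0.8. Over all findings CAD is better throughout, by about 3.2 h falling to 0.5 h.
- CAD 20% faster: significantly slower in 43, 18 and 4% at d = 0.3, 0.4 and 0.5. At d = 0.6 the benefit is declared in only 6%.
- CAD 40% faster: the benefit is declared in 85 to 99% of runs for d from 0.6 to 0.8.

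**The opposite direction.** The Limitations section names false negatives and overreliance. Suppose, under B with unchanged speed, that control finds 60% of hard findings and CAD units only 40%. Detected-only means are 1.78/0.88 = 2.02 h (control) and 1.42/0.82 = 1.73 h (CAD), so CAD looks 0.29 h faster. Over all findings the means are 4.66 h and 5.74 h, so CAD is 1.08 h worse.

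**The case against.** **Findings surfaced by the CAD need not be slow.** The protocol describes predictions within seconds to about a minute, with alerts. If in illustration A the hard findings took 1.5 h, like the easy ones, the observed means would be 1.5 h against 2.0 h, the right direction at any missed share. A reader might infer that a working CAD will look useless or slower. The documents do not support that, because they give no times for missed or difficult findings. This objection stands.

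**Illustration A is extreme.** Control finds no hard case, and 0.30×24 = 7.2 h of its 8.60 h comes from the chosen horizon. This also stands: the 5.35 h is no estimate of the benefit. Illustration B drops the first assumption and the mechanism remains.

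**The rate tests may reveal missed findings.** The chi-square and proportion tests could show a difference in detection or intervention. They would not make the time contrast a comparison of like with like.

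**Details belong in the analysis plan.** A reader might infer that the protocol orders missed cases to be dropped. It does not say so; this follows from the named test and the lack of another rule. Clock start and handling rules can fairly be left to a fuller document. The t test cannot, because the article itself fixes it.

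**The outcomes are secondary.** Promotion of detection time is given only as an example, conditional on the pilot. That limits the weight but does not remove the point.

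**Conclusion.** The concern holds in this form: t tests on detection, repositioning and drain times condition on detection and treatment, which the CAD affects, so the contrast of means is not a randomised comparison. This follows from the named method and needs no assumed figure.

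Direction and size do depend on figures that the protocol does not give: how many findings each arm misses, how slow the extra findings are, and how far the CAD speeds up the rest. The worked cases cover reversal, near-disappearance, the correct sign and bias in the CAD's favour. Reversal is therefore a possibility and should not be presented as the expected result. The matter should be settled before phase 2, and in any case before detection time is considered as primary outcome.

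**What to change.** Under Statistical and Cost-Effectiveness Analysis, replace the t tests for these times by a time-to-event comparison on one risk set defined identically in both arms:

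- **Risk set:** all films flagged by the stored CAD output, which is already generated, hidden, in control units. Do not require confirmation by the routine clinical read. That read is unblinded, and a control finding that nobody noticed would not be confirmed, so the selection would return. Where a patient has several flagged films, starting from the first per finding is sensible, since later films depend on how it was handled.
- **Clock and event:** start at film acquisition. Take clinician recognition or action from the same chart source in both arms, not from the alert time stamp.
- **Incomplete cases:** keep never-detected and never-treated flagged films up to a fixed, prespecified horizon (24 h above is only illustrative). Treat death, discharge and tube removal as competing events.
- **Summary:** restricted mean time, or the share acted on by fixed times, with variance at the unit level.

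**Cost.** This changes the analysis wording and requires CAD outputs and film time stamps to be kept in both arms. It needs no extra patients, readers or procedures.

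**Downside.** The estimand becomes time to action on CAD-flagged films. It includes false flags, which dilute the effect (AUC for ETT misplacement is 0.847 and 0.734 in the two test sets), and it omits findings that the CAD misses. State this as a limitation and keep the analysis of clinically recorded findings as descriptive only. A set of true findings independent of the CAD would need blinded re-reading, hence extra readers and access to images that the protocol says it will not collect.

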### Objective

This study aims to apply the AI-based CAD system for automatic detection and assessment of catheter placement and pneumothorax in emergency and intensive care settings. We aim to evaluate the clinical and economic benefits of the CAD system via rigorous randomized trial without altering routine care and procedures.

In terms of clinical benefits, the study will assess whether the use of the CAD system reduces mortality and will evaluate hospital stay duration, the time required to detect misplacement, and the time needed to reposition ETTs, NGTs, and chest drainage tubes. For the economic evaluation, the study will compare the cost-effectiveness of using the CAD system versus standard care without CAD.

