Data collection included the total number of patients in the ward, the number of patients using ventilators, the number of pneumothorax cases, CXR results, misplacement detection time, mortality rate, length of stay, ETT resetting time, NGT resetting time, pneumothorax drainage tube placement time, direct medical costs (eg, x-ray examinations, intubation fees, and hospitalization fees), and indirect medical costs (eg, CAD system costs and labor costs). The implementation costs are expected to differ between the intervention and control arms. The intervention arm includes additional expenditures related to AI system deployment, such as system infrastructure, routine maintenance, training, and IT support. These costs are captured as part of the economic evaluation to assess whether the clinical benefits of AI-assisted care justify the associated investment. Imaging data will not be collected, and the AI software will not undergo model training.

The inclusion and exclusion criteria for cluster randomized controlled trial.

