Cost-effectiveness analysis will be conducted using TreeAge software to compute the incremental cost-effectiveness ratio. This ratio will assess the additional cost required to achieve one unit of clinical benefit when using the AI system as compared to traditional methods. The incremental cost-effectiveness ratio will be calculated by dividing the cost of the intervention (which includes the medical, AI system, and maintenance costs) by the effectiveness, which will be measured through various clinical outcomes, such as reduced diagnostic time, decreased mortality rates, fewer misdiagnoses, and quality-adjusted life years (QALYs).

QALYs will serve as a composite measure of health outcomes by combining both the quantity and quality of life. The calculation of QALYs will involve multiplying the expected survival years after the intervention by a health state weight, which reflects the patient’s quality of life during those years. This weight ranges from 0 (death) to 1 (perfect health), and negative values may be used to indicate health statuses worse than death.

QALY = Years of Life × Health State Weight

To ensure the robustness of the findings, sensitivity analyses will be conducted, including both simple sensitivity analysis and probabilistic sensitivity analysis. These analyses will account for variability in model parameters and simulate different combinations of parameters to evaluate the stability of the cost-effectiveness conclusions. The results of these analyses will be assessed through acceptance curves and cost-effectiveness planes, which will allow a comparison of the cost-effectiveness of different treatment strategies under various assumptions.

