## Results

The implementation of the AI-assisted CXR CAD system is expected to yield substantial improvements in clinical outcomes and health care efficiency. By enabling timely identification of critical conditions such as misplaced ETT and NGT and pneumothorax, the system is anticipated to reduce in-hospital mortality rates from 28% to 25%. This improvement reflects the system’s potential to facilitate faster recognition of life-threatening situations and prompt clinical interventions.

Moreover, the use of the CAD system is projected to shorten the length of hospital stays, particularly by accelerating the detection of misplaced tubes and pneumothorax, which allows for timely correction and treatment. The time required for specific interventions, such as repositioning ETTs and NGTs or placing drainage tubes for pneumothorax, is also expected to decrease, further enhancing patient care efficiency.

From an economic perspective, the adoption of the CAD system is anticipated to reduce overall health care costs. This includes direct medical costs, such as imaging fees and hospitalization expenses, as well as indirect costs, such as personnel and system maintenance. By improving diagnostic accuracy and reducing delays in treatment, the system is expected to contribute to long-term cost savings while ensuring better health outcomes for patients.

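### The rule for calculating the ICER leaves out the control arm's cost and contradicts the protocol's own description of the ratio as additional cost versus usual methods

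*Protocol article*

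**What the plan says.** The economic aim, in the Introduction under Objective, is comparative: "the study will compare the cost-effectiveness of using the CAD system versus standard care without CAD". In Methods, Statistical and Cost-Effectiveness Analysis, two adjacent sentences then deal with the ICER.

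- The description: "This ratio will assess the additional cost required to achieve one unit of clinical benefit when using the AI system as compared to traditional methods".
- Next, the calculation rule: "calculated by dividing the cost of the intervention (which includes the medical, AI system, and maintenance costs) by the effectiveness".

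The effectiveness measures offered for the denominator are "such as reduced diagnostic time, decreased mortality rates, fewer misdiagnoses, and quality-adjusted life years (QALYs". The same section defines a QALY as years of life multiplied by a health state weight, which is a level for one strategy. It also says how the sensitivity analyses will be presented: "The results of these analyses will be assessed through acceptance curves and cost-effectiveness planes".

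On costs, the Phase 2 section says "The implementation costs are expected to differ between the intervention and control arms" and lists x-ray, intubation and hospitalization fees as direct medical costs. The Results section states the expected direction: "the adoption of the CAD system is anticipated to reduce overall health care costs".

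**The concern.** The description is incremental and the rule is not. The rule's numerator is the cost of the intervention including medical costs. Control patients also incur x-ray, intubation and hospitalization costs, so without subtraction the numerator is the whole cost of care under CAD and not the extra cost of choosing CAD.

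This matters because cost-effectiveness against standard care is one of the trial's two stated purposes. A ratio built on the rule does not answer that question and cannot be read against a willingness-to-pay threshold for additional benefit. It also has no place on a cost-effectiveness plane, whose axes are the differences in cost and effect between strategies. The authors expect CAD to be both cheaper and better. That is a negative cost difference, which a numerator made of total cost cannot express.

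**Working it through.** The document gives no ICER value and no cost amounts, so there is no figure to reproduce. The check compares the described ratio with the two ratios that the rule can produce.

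**Inputs**
- Mortality 28% under standard care and 25% with CAD (Determination of Sample Size; Results). Survival is therefore 0.72 and 0.75, a difference of 0.03.
- Costs are an assumption: control 100 units per patient, CAD from 90 to 110.
- Survival stands in for any effect measured as a level. The documents give no QALY values.

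**Formulas** (C = mean cost, E = mean effect)
- (a) Incremental, as described: (C_CAD − C_control) / (E_CAD − E_control)
- (b) Rule as written, with effectiveness as a difference (reduced time, lower mortality, fewer misdiagnoses): C_CAD / (E_CAD − E_control)
- (c) Rule as written, with effectiveness as a level (QALYs): C_CAD / E_CAD

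| CAD cost | (a) (C_CAD − 100)/0.03 | (b) C_CAD/0.03 | (c) C_CAD/0.75 |
|---|---|---|---|
| 90 (−10%) | −333 | 3,000 | 120 |
| 95 (−5%) | −167 | 3,167 | 127 |
| 100 (0%) | 0 | 3,333 | 133 |
| 105 (+5%) | 167 | 3,500 | 140 |
| 110 (+10%) | 333 | 3,667 | 147 |

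**What the table shows**
1. Ratio (a) changes sign with the cost difference. Ratios (b) and (c) are positive in every row, so neither separates a saving from an added cost.
2. Ratio (b) exceeds (a) by a constant, C_control/(E_CAD − E_control) = 100/0.03 = 3,333. At +5% cost this is 3,500 against 167, or 21-fold.
3. Ratio (c) has no fixed direction of error. Setting C/0.75 = (C − 100)/0.03 gives 0.72C = 75, so C = 104.17. There both ratios equal 138.9. Below that cost (c) is too high (at −10%, 120 against −333). Above it (c) is too low (at +10%, 147 against 333).

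**The case against.** The strongest defence is that the rule is one loosely condensed sentence in a journal article, and everything around it shows incremental intent. The ratio is named as incremental, the sentence just before defines it properly, the Objective sets CAD against standard care, the Phase 2 section expects implementation costs to differ by arm, and cost-effectiveness planes are planned. An analyst working from the whole text would probably subtract the control arm. A fuller economic plan may also exist.

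Much of this stands, and it rules out stronger readings that a reader might draw:
- That the ICER is simply defined as an average ratio. The description is correct, and three of the four listed effect measures are worded as differences, for which the rule gives something other than an average ratio.
- That the economic conclusion will be wrong. That follows only if the rule is applied literally, against its context.
- That the result is always positive. Under the difference reading it would be negative if CAD were less effective.
- That the error has a known size. An assumed cost difference close to zero makes the multiple as large as one likes, and under the level reading the error vanishes at +4.2% and then reverses.

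The defence does not remove the contradiction. The point is not that detail is missing: the article states a formula, and that formula disagrees with the sentence before it. Reading the numerator as only the extra cost of adding CAD is hard to sustain, because the parenthesis expressly includes medical costs.

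**Conclusion.** The rule is wrong as written, at moderate severity, and should be corrected before the economic analysis. Two adjacent sentences contradict each other, and the one that gives the arithmetic omits the comparator's cost. If followed while CAD is the more effective strategy, it returns a positive figure whatever the cost difference, so it cannot show the anticipated saving or correspond to the planned plane.

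That conclusion is algebraic and needs no cost data beyond a positive total cost in the CAD arm. The numerical size does need such data: the figures above rest on assumed costs and on the protocol's projected mortality, and illustrate the behaviour without estimating the error to be expected. Randomisation, data collection, sample size and the primary analysis are unaffected.

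**What to change.** Replace the calculation sentence with one that agrees with the description before it:

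ICER = (mean cost CAD − mean cost control) / (mean effect CAD − mean effect control)

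Apply it to each effect measure, with QALYs entering as the between-arm difference.

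Add one sentence for cases where a ratio is uninformative. If the cost difference is negative, or the effect difference is near zero, report dominance (the quadrant of the plane) or incremental net benefit, that is, threshold × effect difference − cost difference. This is needed because a negative ICER is ambiguous: in the illustration, −10/0.03 (cheaper and better) and 10/(−0.03) (dearer and worse) both equal −333.

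The cost is one formula and a line or two of wording. Costs and outcomes are already to be collected in both arms, so no new data are needed, and the change can be made at any time before the economic analysis.
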